## Abstract

**Background:**

Patients with recent stroke or TIA are at high risk for new vascular events. Several evidence based strategies in secondary prevention of stroke are available but frequently underused. Support programs with multifactorial risk factor modifications after stroke or TIA have not been investigated in large-scale prospective controlled trials so far. INSPiRE-TMS is a prospective, multi-center, randomized open intervention trial for intensified secondary prevention after minor stroke and TIA.

**Methods/design:**

Patients with acute TIA or minor stroke admitted to the participating stroke centers are screened and recruited during in-hospital stay. Patients are randomised in a 1:1 ratio to intervention (support program) and control (usual care) arms. Inclusion of 2.082 patients is planned. The support program includes cardiovascular risk factor measurement and feedback, monitoring of medication adherence, coaching in lifestyle modifications, and active involvement of relatives. Standardized motivational interviewing is used to assess and enhance patients’ motivation. Primary objective is a reduction of new major vascular events defined as nonfatal stroke and myocardial infarction or vascular death. Recruitment time is planned for 3.5 years, follow up time is at least 2 years for every patient resulting in a total study time of 5 years (first patient in to last patient out).

**Discussion:**

Given the high risk for vascular re-events in acute stroke and the available effective strategies in secondary prevention, the INSPIRE-TMS support program has the potential to lead to a relevant reduction of recurrent events and a prolongation of the event-free survival time. The trial will provide the basis for the decision whether an intensified secondary prevention program after stroke should be implemented into regular care. A cost-effectiveness evaluation will be performed.

**Trial registration:**

clinicaltrials.gov: 01586702

## Background

Patients with recent stroke or TIA are at high risk for a recurrent stroke or other major vascular events [1-4]. Despite this high risk and the availability of evidence based secondary prevention strategies, risk factor control and medication adherence frequently remain under recommended targets [5].

This observation has a variety of reasons: Although at much higher risk, post-stroke patients do often not receive more intensive medical care than patients in primary prevention [4,6]. The separation of health systems in hospital-based and outpatient care as in Germany is a major barrier for optimal secondary prevention as recommendations given in the acute stroke facility are frequently not followed by primary care physicians (in part depending on their specialty) [4]. Another problem is that despite a high motivation for optimal secondary prevention shortly after experiencing the initial cerebrovascular event, many patients don’t stick with the recommended measures over a longer time period. One-third of stroke patients discontinue secondary prevention medication [7] and control of arterial hypertension as the most important risk factor for stroke remains unsatisfactory across countries [4,8].

Positive experiences with structured support programs have been gained in other diseases such as diabetes mellitus [9], coronary heart syndrome [10,11] and arterial hypertension [12] yielding better quality of risk factor control and remarkable reductions in clinical event rates [10,13].

Considering the typical stroke and TIA population which consists mainly of elderly patients frequently having multiple risk factors and a high risk for dependency after a recurrent event, a structured supported secondary prevention program after stroke appears promising. However, it has never been tested in an adequately powered trial. As a consequence, stroke has not been selected for chronic disease management programs.

A recent observation strengthens the hypothesis that patients with cerebrovascular disease are likely to benefit from a multimodal secondary prevention scheme. Intensified medical treatment in patients with symptomatic arterial stenosis (forming the control arm and compared against stenting) was associated with a more than 50% lower recurrence rate in the SAMMPRIS trial [14] compared to patients with the same inclusion criteria but non supported secondary prevention in the WASID trial [15]. However this effect was not observed in a face-to-face trial but in a comparison with a historical cohort.

The INSPiRE-TMS trial is therefore designed to evaluate the effects of a structured support program focussing on cardiovascular risk factor control, monitoring of medication adherence, coaching in lifestyle modifications, and active involvement of relatives over a period of at least 2 years.

## Methods/design

### Study design

INSPIRE is a prospective, multi-center, randomized open intervention trial for intensified secondary prevention initiated and coordinated by the Center for Stroke Research Berlin. Approval was obtained by the local ethics committee (EA2/084/11). The study has been registered at the trial registration (clinicaltrials.gov: 01586702).

### Objectives

*Primary objective:* With regard to new vascular events the study shall prove that the participation in a patient-centered intensified secondary prevention program increases the event-free survival time during follow up compared to the participation in usual care.

Secondary objectives:

To improve risk factor control and adherence to medical recommendations

To evaluate the effect of optimized secondary prevention on surrogate parameters such as physical fitness, vascular changes on retinal fundus and silent vascular lesions in MRI

To evaluate the influence of body weight and other metabolic parameters on vascular event rates in secondary prevention

To calculate the cost-effectiveness of the support program.

### Participants

Acute patients with TIA (clinical restitution within 24 hours and ABCD2-Score ≥3 or visible DWI-lesion in MRI) or minor stroke (mRS ≤ 2 at time of screening and visible DWI-lesion in MRI) evaluated in a dedicated and organized setting of care (Stroke Unit, out-patient clinic) in Germany and Denmark will be included in the study. Participating study centres are the Departments of Neurology at the Charité-University Medicine Berlin, Campus Benjamin Franklin, Campus Virchow-Klinikum and Campus Mitte, the Department of Neurology, Klinikum rechts der Isar at the Technische Universität of Munich, the Department of Neurology at the Klinikum Ludwigshafen (all in Germany), and the Department of Neurology at the University of Aarhus, Denmark.

*Inclusion criteria:* Age over 18 years; acute stroke or TIA within 14 days prior to inclusion into the study; at least one of the following risk factors: arterial hypertension, diabetes mellitus, atrial fibrillation and/or smoking; written informed consent, and realistic perspective in keeping the outpatient appointments.

*Exclusion criteria*: Distance from home to study center not in suitable range for keeping the outpatient appointments, cognitive impairment jeopardizing adherence to the support program, modified Rankin Score >2 at time of study inclusion, malignant disease with life expectancy of less than 3 years, relevant alcohol or other substance abuse (except for nicotine), stroke or TIA aetiology without options for evidence based secondary prevention (e.g. dissection or vasculitis).

### Recruitment and randomization

Consecutive acute patients with TIA or minor stroke admitted to the Stroke Units or TIA clinics of the participating centers will be included during in-hospital or in-clinic stay. Patient recruitment is planned over a 3.5-years period. Follow-up is planned for a minimum of 2 years for every patient after study inclusion in order to complete the 2 years intervention program in all patients. Therefore the study time from first patient in to last patient out is 5 years in total.

After approval from the participants and completion of the initial assessment, patients will be formally entered into the study and randomized with a 1:1 randomization to intervention and control arm by a web-based online randomization procedure provided by the Coordination Center for Clinical Studies (KKS) at the Charité.

### Procedures

Study procedures are depicted in the flow chart (Figure 1).

**Figure 1 F1:**
[figure not shown]
Flow chart of study procedures.

*Standardized baseline assessment* for intervention and control groups will include a questionnaire regarding demographic information, risk factors and co-morbidities, clinical symptoms of the acute cerebrovascular event, and duration of symptoms.

*Standard clinical evaluation* will consist of a neurological examination according to the National Institutes of Health Stroke Scale (NIHSS) at admission and modified Rankin Scale (mRS) as well as Barthel Index (BI) at time of study inclusion. Stroke aetiology will be classified according to TOAST criteria [16]. Laboratory measures will include LDL cholesterol, CRP, HbA1c, and INR. Body mass index (BMI, kg/m2) will be calculated from height and weight measurements. Blood pressure will be measured manually in sitting patients (resting at least 5 min) on both arms. Both blood pressure values will be recorded and the higher value will be used for statistical comparisons. Arterial hypertension is defined by either repeated elevated systolic blood pressure >140 and/or diastolic blood pressure >90 mm Hg or the previous use of antihypertensive drugs. Diabetes is defined by either HbA1c ≥6.5% or use of antidiabetics. Hyperlipidemia is defined by either LDL cholesterol > 100 mg/dl or use of lipid-lowering drugs. Smoking will be evaluated in number of cigarettes per day and in pack years. Patients who currently don’t smoke will be divided in non-smokers and past smokers (within the last 5 years). The time since smoking cessation will be documented. Physical activity is measured as frequency of “physical activity with an intensity leading to transpiration and/or elevated breathing frequency over more than 30 min” per week. Detailed and structured information concerning vascular risk factor targets will be given to the patients before discharge and these recommendations will be included in the discharge letter to primary care physicians (PCP) irrespective of the trial allocation.

*Standard care* will consist of outpatient care usually guided by a primary care physician. The treating primary care physician will be informed about the results of risk factor measurements at the yearly follow-up appointments but no further recommendations will be given to the patient or PCP by the study team.

#### Intervention program

The target values for secondary prevention are orientated at the recommendations of the German Society of Neurology respective the European Stroke Organisation. For patients with high recurrence risk in large vessel disease (see above), targets are adapted on the basis of “aggressive medical treatment” of the SAMMPRIS trial [14].

The intensified support program is planned with a total of eight outpatient appointments. The structured assessment will include risk factor control, medication intake, compliance with oral anticoagulation therapy (including monitoring of INR in Vitamin K antagonist treatment) and joint agreement on an individual target plan.

Target values for risk factors are:

Blood pressure <140/85 mmHg (<130/80 in diabetic patients) [16]

Physiological circadian blood pressure with >10% lower BP values during nighttime

HbA1c <7.5%

Nicotine abstinence

LDL <100 mg/dl in patients with arterial or cardioembolic stroke without specifically elevated risk, LDL ≤70 mg/dl with CHD, LDL ≤70 mg/dl in patients with symptomatic intracranial stenosis judged as hemodynamically relevant (independent from examination technique) or extracranial stenosis >50% according NASCET criteria without surgical intervention, LDL ≤70 mg/dl in patients with evidence of instable plaque (in plaque imaging) in the corresponding extracranial artery

Physical activity ≥30 min per day at least three times per week (oriented at the recommendations of the German Society of Neurology

Healthy nutrition (intake of 4–5 portions of fruit and/or vegetables per day)

The targets for pharmaceutical treatment are:

Platelet inhibitors for all patients with Stroke/TIA caused by small or large vessel disease

Dual antiplatelet therapy over three months in patients with symptomatic intracranial stenosis judged as hemodynamically relevant (independent from examination technique) or extracranial stenosis >50% (according NASCET) without surgical intervention or in patients with evidence of instable plaque (in plaque imaging) in corresponding extracranial artery

Oral anticoagulation (INR 2–3) or regular intake of new oral anticoagulants in patients with atrial fibrillation

Statin treatment (Simvastatin 40 mg or Atorvastatin 80 mg) in patients with LDL >100 mg/dl or LDL ≤70 mg/dl in patients with high recurrence risk.

Intervention strategies:

Comprehensive and repeated information about pathophysiology of the individual risk for recurrent event of stroke or TIA and potentials of vascular risk reduction. This information will be offered to the patients during in-hospital stay but also as part of the outpatient appointments. Next of kin will be involved as much as possible.

An individual plan regarding target values and medication will be agreed upon with the patient using methods of motivational interviewing

The patient’s motivation will be enhanced using feed-back-strategies regarding measured risk factors, target measurements (e.g. INR) and “memory parameters” such as HbA1c or physical fitness

Complementary offers: assistance in finding peer groups and group therapies (e.g. nordic walking, INR self measurement and smoking cessation programs).

Required certificates and training for involved professionals and treatment algorithms:

Patients will receive counseling by board certified physicians with special training in neurovascular medicine at all intervention appointments. Preparation for medical counseling by assessment of risk factor control can be performed by trained nurses or healthcare assistants.

A standardized motivational interviewing training over 2 days and reinforcement training over one day after approximately 6 months is compulsory for all physicians involved in counseling during appointments in the support program.

Standard operating procedures are used for concrete action in case of critical deviations from target values regarding blood pressure and anticoagulation.

Information about risk factor control is communicated to family doctors via standardized reports including telephone conversation in case of urgently needed action or aimed interdisciplinary consensus.

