### Study endpoints

#### Primary endpoint

Composite of non fatal stroke (including strokes with new tissue-based definition), non fatal major coronary event and cardiovascular death.

Secondary endpoints:

Rate of patients who meet the recommended guideline targets regarding blood pressure, smoking cessation, serum-LDL, physical activity, HbA1c (in patients with diabetes), therapeutic range of INR or regular intake of new oral anticoagulants in patients with atrial fibrillation,

Effects on vascular surrogate parameters (microalbuminuria, physical fitness,)

Total mortality

Frequency of hospital admissions for vascular diseases (including TIA, angina pectoris with vascular interventions, peripheral arterial occlusive disease with vascular intervention)

Number of days “alive and at home”.

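### Minor error: the statin line gives the LDL target (≤70 mg/dl) as the treatment criterion for high-recurrence-risk patients, so as worded it skips those above 70 and up to 100 mg/dl

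*Protocol article*

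**What the plan says.** All the relevant statements on LDL and statins stand in the protocol article under Intervention program.

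- **Approach for high risk.** "For patients with high recurrence risk in large vessel disease (see above), targets are adapted" from the aggressive medical arm of an earlier trial that compared such treatment with stenting.
- **LDL target, ordinary risk.** "LDL <100 mg/dl in patients with arterial or cardioembolic stroke without specifically elevated risk".
- **LDL target, large-vessel high risk.** "LDL ≤70 mg/dl in patients with symptomatic intracranial stenosis judged as hemodynamically relevant". The same ≤70 mg/dl value is set for unoperated extracranial stenosis above 50% and for unstable plaque.
- **Statin line, under the drug-treatment targets.** Simvastatin 40 mg or atorvastatin 80 mg "in patients with LDL >100 mg/dl or LDL ≤70 mg/dl in patients with high recurrence risk".

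Among the secondary endpoints, the article lists "Rate of patients who meet the recommended guideline targets regarding blood pressure, smoking cessation, serum-LDL" and further targets.

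**The concern.** A treatment threshold and a treatment target normally carry opposite signs: one treats above a value in order to get to or below it. The first half of the statin line follows this pattern (target below 100, treat above 100). The second half keeps the sign of the target (target ≤70, treat at ≤70). Both halves are joined by *or* as descriptions of the patients to be treated, so the clause for high-risk patients picks out those who have already reached the goal.

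The line is one of the drug-treatment targets of the experimental programme, and it concerns patients given the strictest LDL goal. Anyone who delivers or replicates the programme from this text would find a statin criterion that, as worded, does not serve that goal. At stake is clear delivery of one intervention component, not the analysis.

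**Working it through.** The plan gives no figure to reproduce, so this is a check of the rule's logic against the target.

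**Inputs (all from Intervention program)**

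- Target for high-recurrence-risk patients: LDL ≤70 mg/dl.
- Statin rule as worded for these patients: LDL >100, or LDL ≤70. The first clause is taken to apply to every patient, high-risk or not.
- Corrected rule for these patients: LDL >100, or LDL >70, which reduces to LDL >70.

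**High-risk patients at test values of LDL (mg/dl)**

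| LDL | Distance above target (LDL − 70) | At target? | Statin, as worded | Statin, corrected |
|---|---|---|---|---|
| 60 | none | yes | yes | no |
| 70 | 0 | yes | yes | no |
| 71 | 1 | no | **no** | yes |
| 85 | 15 | no | **no** | yes |
| 99 | 29 | no | **no** | yes |
| 100 | 30 | no | **no** | yes |
| 101 | 31 | no | yes | yes |
| 130 | 60 | no | yes | yes |

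The wording fails in the band 70 < LDL ≤ 100. At its upper end the reduction needed to reach target is (100 − 70)/100 = 30%. This is the only band in which the stricter ≤70 target could add statin indications beyond the general >100 clause, so as worded the high-risk clause adds none where they are needed. With the corrected rule, every off-target value in the table carries an indication.

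**Ordinary-risk patients.** Target (<100) and treatment criterion (>100) agree at every test value except exactly 100 mg/dl, a boundary point of no practical weight.

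**Could the sign be a text-extraction fault?** Unlikely. The symbol ≥ is rendered correctly elsewhere (ABCD2 score ≥3, HbA1c ≥6.5%, activity ≥30 min), the > sign appears in the same line, and ≤70 matches the target entries.

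**Does another statement supply the rule?** None shown does. The definition of hyperlipidemia under Procedures uses LDL above 100 mg/dl or use of lipid-lowering drugs, so it gives no trigger for an untreated patient at 71 to 100. The standard operating procedures for critical deviations, under Intervention program, name blood pressure and anticoagulation, not LDL.

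**The case against.** The strongest reply is that context settles the meaning. The line stands under a list of treatment targets, and ≤70 repeats a value already given as the LDL goal in the same section. A rule that treats an LDL of 60 and leaves 85 untreated is one no physician would apply. Counselling is by board-certified physicians with neurovascular training, and "An individual plan regarding target values and medication will be agreed upon with the patient". A high-risk patient at 85 mg/dl would be seen as off target whatever the statin line says. The natural reading is a compressed instruction to give a statin and bring LDL to ≤70 mg/dl.

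Most of this stands, and it is why the point is minor. It does not make the sentence correct: the article states a criterion and states it wrongly, which is different from leaving detail to a fuller protocol.

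Three stronger readings are tempting, and the documents support none of them.

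- A reader might infer that high-risk patients will in practice go without a statin, lowering LDL target attainment or weakening the trial's treatment effect. That would require physicians to follow the literal wording against the target in the same section, and nothing shown suggests they would.
- A reader might infer that the intended rule is wide open. Treating above 70, treating to reach ≤70, and treating every high-risk patient all close the 70 to 100 gap. They can differ only for patients already at or below 70, so nothing is left open for the patients at issue.
- A reader might infer that patients with coronary heart disease fall outside the rule. The article gives them their own ≤70 mg/dl target, and how the statin trigger is applied to them is treatment-algorithm detail that an article may leave to the full protocol.

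**Conclusion.** The statin line is wrong as written, and the error is minor. For high-recurrence-risk patients it names the target as the criterion for treatment. Read literally, LDL above 70 and up to 100 mg/dl is off target by as much as 30 mg/dl without a statin indication, while patients already at target are selected. This contradicts the ≤70 mg/dl goal and the intensified approach that the same section states for this group.

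The conclusion rests on taking both clauses as patient criteria, which is how the sentence is built. The article does not say how many patients would fall in the band, so no effect on delivery or results can be sized, and none is claimed.

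The analysis is untouched. The effect size behind the sample size comes from blood pressure reduction alone (Power and sample size calculation). The primary analysis is a Cox model for time to vascular events (Statistical analysis). The LDL part of the secondary endpoint is scored against the recommended targets, not against the statin line (Study endpoints).

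**What to change.** Reword the criterion so that a statin (simvastatin 40 mg or atorvastatin 80 mg) is given when LDL is >100 mg/dl, or when LDL is >70 mg/dl in a patient at high recurrence risk. Stating instead that in high-risk patients the statin is given to reach LDL ≤70 mg/dl closes the same gap.

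The cost is one corrected phrase. Visits, sample size, endpoints and analysis stay as they are.

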### Statistical analysis

The primary analysis is a time to event analysis using Cox-regression-models. An interim analysis after 160 observed events will be done by a statistician blinded to the study arm. The interim analysis will indicate whether the sample size and study duration has to be modified according to the overall observed event rate. The sample size needs not to be adjusted for this blinded interim analysis as only the overall event rate will be considered. The assessment of the true drop out rate will be part of the (blinded) interim analysis. The dichotomized secondary endpoints will be evaluated according to the primary outcome measure. Continuous variables will be analyzed with the appropriate tests. The clustering of the data by the different centres will be accounted for by using frailty models [20].

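### Centre is the only clustering level named, but study physicians counsel only the intervention arm; if outcomes vary by physician, tests of risk-factor target attainment will be too liberal

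*Protocol article*

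**What the plan says.** All references are to the protocol article.

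- **Delivery (Intervention program).** "The intensified support program is planned with a total of eight outpatient appointments". On who counsels: "Patients will receive counseling by board certified physicians with special training in neurovascular medicine at all intervention appointments". The method is motivational interviewing, and training is common to all: "A standardized motivational interviewing training over 2 days and reinforcement training over one day after approximately 6 months is compulsory for all physicians". Standard operating procedures cover critical deviations in blood pressure and anticoagulation.
- **Control arm (Procedures, standard care).** Follow-up is with the primary care physician, who is told the yearly risk-factor results, but "no further recommendations will be given to the patient or PCP by the study team".
- **Endpoint (Study endpoints).** The first secondary endpoint is "Rate of patients who meet the recommended guideline targets regarding blood pressure, smoking cessation, serum-LDL, physical activity", with HbA1c and anticoagulation control also listed.
- **Analysis (Statistical analysis).** "The clustering of the data by the different centres will be accounted for by using frailty models". Dichotomised secondary endpoints are to follow the primary outcome's analysis. No other level of clustering is named.
- **Not stated.** The number of counselling physicians, the patients per physician, any ICC, the significance level, and whether a patient keeps the same physician over the eight visits.

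**The concern.** Patients coached by the same physician may resemble each other in whether they reach their targets. Only intervention patients have such a physician, so any such correlation sits in one arm. The analysis section recognises that observations may be dependent, but names a level that both arms share. A shared centre effect raises or lowers both arms together and drops out of the within-centre contrast. One-arm physician variation stays in that contrast. Even with one physician per centre it remains, as a centre-by-arm difference.

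The endpoints most exposed are those the physicians coach directly: blood pressure, LDL, smoking and activity. If physicians differ, the confidence intervals for these would be too narrow, and the results of a few effective or ineffective physicians could be read as a property of the programme.

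**Working it through.** **1. The plan's own figure.** The article gives no calculation for target attainment, so only the primary sample size can be reproduced. Inputs (Power and sample size calculation): control rate 16.94%, relative reduction 28%, hence 16.94% × 0.72 = 12.20%; power 80%; non-adherence 10%; drop-out 5%. A two-sided 5% level is assumed.

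n per arm = [1.96·√(2·p̄·(1−p̄)) + 0.842·√(p1(1−p1) + p2(1−p2))]² / (p1−p2)² = (0.978 + 0.419)² / 0.0474² ≈ 868.

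868 / 0.95 / 0.90 ≈ 1,016 per arm, or 2,032 in total. That is 2.4% below the stated 2,082; with a continuity correction the total is 2,128, 2.2% above it. The stated figure is thus consistent with a two-sided 5% level, which is used below.

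**2. Inputs for target attainment.**
- Patients analysed per arm: 1,041 × 0.95 ≈ 989.
- Physicians K, intervention arm only: not stated; 12 to 36 assumed.
- Physician ICC: not stated; 0, 0.01 and 0.02 assumed.

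**3. Formulae.**
- Patients per physician: m = 989 / K.
- Design effect, intervention arm: DE = 1 + (m − 1) × ICC. Control arm: 1.
- True over naive standard error of the arm difference: r = √[(DE + 1) / 2].
- Actual error of a nominal 5% test: 2 × [1 − Φ(1.96 / r)].

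Example, K = 12 and ICC 0.02: m = 82.4; DE = 1 + 81.4 × 0.02 = 2.63; r = √(3.63 / 2) = 1.347; 1.96 / 1.347 = 1.455; error 14.6%.

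| K | m | ICC 0 | ICC 0.01 | ICC 0.02 |
|---|---|---|---|---|
| 12 | 82.4 | 5.0% | 9.8% | 14.6% |
| 24 | 41.2 | 5.0% | 7.4% | 9.8% |
| 30 | 33.0 | 5.0% | 6.9% | 8.8% |
| 36 | 27.5 | 5.0% | 6.6% | 8.1% |

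**4. Does adjusting for centre remove it?** No. Simulation with six centres, 40% attainment (assumed) and a centre-stratified contrast gave 14.5% for 12 physicians at ICC 0.02 and 7.2% for 30 physicians at ICC 0.01. Random rotation of patients among a centre's physicians over eight visits left 15.3% for 12 physicians at ICC 0.02.

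**5. How small must the ICC be?** The error reaches 6% at an ICC of about 0.002 with 12 physicians and about 0.005 with 30.

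**6. Primary endpoint.** The design assumptions imply about 1,041 × (0.1694 + 0.1220) ≈ 303 events. With 300 events and an assumed physician standard deviation τ on the log hazard, the variance of the log hazard ratio is 4/300 + τ²/K. For K = 12 the error is 5.7% (τ = 0.1) to 8.0% (τ = 0.2); for K = 36 it is 5.2% to 6.0%.

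**The case against.** **The document makes no outright error.** This is a condensed article, and a physician-level term could stand in an analysis plan that is not shown. Naming centre does not exclude other levels, and a frailty model with a centre-by-treatment effect would absorb much of the physician variation. This stands as a limit on how strongly the point can be put. It does not remove it: the article states a choice of clustering level, and the natural reading of centre frailty is an effect shared by both arms.

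**The inflation is conditional.** A reader might infer that the standard errors simply are too small and that the false-positive rate exceeds 5%. The article does not support that. It gives neither the number of physicians nor an ICC, and with ICC 0 the test is valid. The null at issue is also a particular one: no average effect, yet real differences between physicians. At 50% attainment an ICC of 0.02 means a between-physician standard deviation of √(0.02 × 0.25) ≈ 7 percentage points, so about half the physicians would do worse than usual care. Common training and operating procedures should reduce such differences. They would, however, have to bring the ICC almost to zero, and the article offers no evidence that they do.

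**The stakes are limited.** A reader might infer that the case for introducing the programme into regular care is undermined. In the abstract's discussion that case rests on recurrent events and event-free survival, not on target attainment.

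**A careless remedy would not work.** Physician-clustered robust variance without a few-cluster correction left about 9% to 10% error with 12 physicians at ICC 0.01 to 0.02, and 6.7% at ICC 0. This stands, and the fix takes account of it.

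**Conclusion.** The point holds in conditional form, for the target-attainment secondary endpoints. Delivery by study physicians in one arm makes the trial partially nested, and a centre effect common to both arms does not represent that. If the physician ICC is 0.01 to 0.02 with 12 to 36 physicians, a nominal two-sided 5% test has an error of about 7% to 15% against a null of no average effect; with ICC 0 it is 5%. The ICC, the number of physicians and the 5% level are all assumptions.

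It would be wrong to read this as a fault in the primary analysis or the sample size. On the assumed inputs the error for the primary Cox analysis is 5.2% to 8.0%, the upper end needing only 12 physicians and the larger assumed standard deviation, and nothing here challenges the 2,082. The change is still worth making, because it is cheap and the physician's identity may be hard to reconstruct later.

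**What to change.** 1. Record the counselling physician's ID at every intervention appointment.
2. Analyse the target-attainment endpoints with a physician random effect in the intervention arm only, in addition to centre. Alternatively, use variance clustered on physician, each control being his or her own cluster, with a few-cluster correction (small-sample factor and t reference distribution). In simulation with 12 physicians this brought the error to about 4% to 6%.
3. Pre-specify how patients who see several physicians are handled, for example by a multiple-membership model. Assigning each patient to the physician seen most often is not enough if patients rotate: uncorrected clustering on that physician left 10.7% error with 12 physicians and 9.8% with 24.
4. For the primary Cox model, use the same approach as a pre-specified sensitivity analysis only.

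The cost is one data field, a few sentences in the analysis plan, and somewhat wider intervals for the target-attainment endpoints. The sample size does not change.
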